## Abstract

**Background:**

Transition in care is defined as the “purposeful and planned movement of adolescents and young adults with a chronic medical condition from pediatric to adult-oriented healthcare systems/care providers.” Currently, there are no Level 1 evidence-based interventions to improve the care of transitioning adolescents and young adults (AYAs) with inflammatory bowel disease (IBD). The development of a transition program using a biopsychosocial approach will improve the standards for healthcare delivery to transitioning IBD patients. This is a protocol for a structured randomized controlled trial (RCT) to assess the clinical and implementation effectiveness of a multimodal intervention focused on improving patient function, transition readiness and outcomes among AYA patients with IBD being cared for at pediatric centers in Canada.

**Methods:**

This multi-center RCT is a type 1 hybrid effectiveness-implementation trial to evaluate effectiveness of the intervention and how it can be implemented more widely after the trial. We will include patients aged 16.0–17.5 years. The intervention program consists of 4 core components: (1) individualized assessment, (2) transition navigator, (3) virtual patient skills-building with a focus on building resilience, self-management and self-efficacy, and (4) a virtual structured education program. The control group will undergo standard-of-care defined by each participating center. The primary outcome will be the IBD Disability Index, a validated measure to assess patient functioning. Secondary outcomes include transition readiness and success, anxiety and depression scales, and health service utilization rates. Additionally, we will measure implementation outcomes and related barriers and facilitators for the intervention program.

**Discussion:**

The type 1 hybrid effectiveness-implementation design will allow for the development of a feasible, sustainable, and acceptable final intervention model. The intervention will consist of modules that can be accessed in an online, virtual platform. The implementation will allow centralization of interventions and funding in order to minimize the impact on local clinical practice or hospital resources. The authors anticipate that the main study limitation will relate to study subjects not completely adhering to every component of the intervention, which will be evaluated and addressed using the implementation science approach.

***Trial registration*:**

NCT05221281. Registry: ClinicalTrials.gov. Date of registration: February 2, 2022. https://clinicaltrials.gov/ct2/show/NCT05221281.

**Supplementary Information:**

The online version contains supplementary material available at 10.1186/s12876-022-02307-9.

## Background

### Transition from pediatric to adult care in adolescents and young adults with IBD

Transition in care is defined as the “purposeful and planned movement of adolescents and young adults with a chronic medical condition to adult-oriented healthcare systems/care providers” [1]. Children in Canada transition from pediatric to adult healthcare services between the ages of 14 and 18, with ultimate transfer to adult care by age 18. There are inherent differences between pediatric and adult care models; pediatric care is family focused, multidisciplinary, and has caregiver involvement for consent and guidance, while adult care is often a single provider and advocates for patient independence [2, 3].

Canada has amongst the highest rates of pediatric-onset inflammatory bowel disease (IBD) in the world [4]. The 2018 Impact of Inflammatory Bowel Disease in Canada Report [5] suggested that childhood-onset IBD is being diagnosed more frequently in Canadian children, increasing 50% in the first decade of the twenty-first century. Children with pediatric-onset IBD face unique challenges. Firstly, pediatric-onset IBD is more extensive, affecting more areas of the gastrointestinal tract [6]. The disease tends to be more inflammatory in nature resulting in lower surgical rates but greater need for immune suppressing medications to maintain remission [7]. As such, the direct costs of pediatric IBD to the health system are significantly higher [8]. In addition, living with a chronic disease can result in significant mental health difficulties in children and adolescents [9]. IBD, in particular, is associated with anxiety and depression [10, 11]. Finally, the onset of disease occurs at a particularly sensitive developmental period in the life of a child. The patient is tasked with developing a sense of self and independence from family while managing a difficult chronic disease [7]. This can interfere with typical developmental milestones that are important to support transition skills [12, 13].

In Canada, care to children and adolescents with IBD is almost exclusively provided by pediatric gastroenterologists, most of whom are affiliated with academic pediatric hospitals [14]. Many adult gastroenterologists have solo or group-based practice with limited multidisciplinary support [15]. Despite transition for adolescents and young adults (AYAs) being identified as a health services priority area [16], there is no standardization for transitioning adolescents with IBD in Canadian pediatric centers.

In light of the medical, psychosocial and health system burdens placed on AYAs with IBD during their transition from pediatric to adult care, an effective transition program could address the unique challenges described above and improve overall outcomes.

### The problem of implementation

While the methodology used to conduct clinical research has advanced, our ability to implement evidence-based practices has not kept pace. Approximately half of evidence-based practices ever reach widespread clinical use [17]. Implementation science aims to bridge the gap between the research-based demonstration of intervention effectiveness and effective and sustainable implementation in clinical practice or community settings. The proposed study is a *Hybrid Type 1* design that assesses both the effectiveness of the implementation strategy, and the health impact of the intervention [18]. *Hybrid Type 1* designs are typically used when the evidence for the effectiveness of the intervention is weak, and test the health impact of the intervention while explicitly collecting data on the implementation process to facilitate subsequent implementation efforts. The proposed study is a *Hybrid Type 1* design, acknowledging the lower quality evidence to support intervention in transition-aged patients with complex chronic disease while understanding the need for more robust data pertaining to IBD.

## Methods/design

This manuscript describes a protocol for a randomized controlled trial (RCT). We have reported details as per the SPIRIT reporting guidelines for RCT protocols [19].

### Purpose

**Aim 1** We will develop and evaluate the clinical effectiveness of a multimodal intervention consisting of 4 core components:Individualized assessment of the AYA’s biopsychosocial needs.The involvement of a transition navigator to facilitate the transition process and further identify and act upon the needs of the individual patient.Patient skills-building exercises to improve areas of need, with particular focus on resilience, self-management, and self-efficacy.Structured online eLearning program to build patient knowledge about the transition from pediatric to adult care and living with IBD as a chronic disease.

**Aim 2** We will evaluate implementation outcomes and contextual factors that hindered or facilitated delivery of the intervention to inform subsequent scale up of the intervention.

### Study design

The proposed study is a multi-center unblinded RCT of AYAs with IBD transitioning from pediatric to adult care. The intervention will consist of 4 core components while the control arm will be the typical approach to transition currently used in each participating Canadian IBD center. Participating sites include: The Hospital for Sick Children (SickKids)(Toronto, Ontario, Canada), Children’s Hospital of Eastern Ontario (CHEO)(Ottawa, Ontario, Canada), BC Children’s Hospital (Vancouver, British Columbia, Canada), and McMaster Children’s Hospital (Hamilton, Ontario, Canada). Additional sites may be added at a future date.

### Participants

See Fig. 1 for patient flow.

**Fig. 1 Fig1:**
[figure not shown]
Patient flow

Inclusion criteria: We will enroll adolescents aged 16–17.5 years with IBD diagnosed > 6 months before recruitment using standard criteria [20]. Since most adolescents are transferred to adult care around 18 years of age, this would allow for at least one year of post-transfer follow-up due to the 3-year length of the grant funding. Study participants must have the ability to speak/read English at a functional (Grade 8) level, intention to reside in Canada after transfer to adult care, and ability to use a smartphone or personal computer for the virtual intervention components. In Canada, > 95% of adolescent IBD patients in Canada have access to technology to complete study requirements [21, 22].

Exclusion criteria: Adolescents who do not fluently speak English, those intending to leave Canada after graduation from high school, and those unwilling to be involved will be excluded. We will maintain a record of ineligible patients, and those who declined enrollment and the reasons for doing so, to inform the feasibility of post-RCT implementation in clinical practice.

### Withdrawal criteria

It is not anticipated that any adverse events will occur as a result of study intervention. Participants who request study withdrawal will be removed and a withdrawal interview conducted to understand the reason for their study withdrawal. Non-adherence to the study intervention will be part of the data collected and analyzed and will inform program rollout.

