### Statistical analysis

The primary outcome is the IBD-DI ordinal measure at the end of the treatment period (1–2 years after transfer). We will compare groups using the Wilcoxon-Mann–Whitney test, and statistical significance set at P < 0.05.

Secondary outcome measures will be analyzed at study completion and interim time points by comparing participants in the intervention and control arms using Wilcoxon-Mann–Whitney test. In addition, repeated measures analysis will determine changes over time for the primary and secondary outcome measures at three timepoints (baseline, time of transfer, end of study).

Assessment of health services outcomes will be conducted by linking clinical to health administrative data. Likelihood of emergency department use and hospitalization after transfer will be compared using multivariable logistic regression analysis. Number of ED and outpatient visits will be determined using either Poisson regression or negative binomial regression. All models will include confounders reported in Canadian health services studies of IBD patients: age at diagnosis, age at transfer, sex, rural/urban household, and socioeconomic status.

Assessment of implementation outcomes will be determined using mixed methods (quantitative and qualitative) assessment, as described above.

Sample size calculation: The IBD-DI ranges in score from 0–100. The categories of disability are 0–20 (no disability), 20–35 (mild disability), 35–50 (moderate disability), and 50–100 (severe disability). In the original validation study of the IBD-DI, the mean score of patients was 35.3 ± 20.5. We would consider the goal of this transition program to allow AYAs to achieve a mean level of < 20 (no disability), presenting a 16-point decrease from the mean baseline, or a Cohen effect size (*d*) of 0.78.

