Assuming alpha-probability of 0.05, 46 patients would be required to achieve a power of 80% (23 in each group), and 62 patients would be required to achieve a power of 90% (31 in each group) (calculated using G*Power version 3.1.9.7). Assuming a drop-out rate of 25% in each group over the course of the study, we will aim to enroll 90 participants (45 in each group). This calculation is likely an underestimation of the study’s power. Two simulation studies have demonstrated that stratified randomization increases study power in trials with sample sizes < 100 [48, 49]. There is no established method for sample size calculation that accounts for stratified randomization [50]. We will limit enrollment to 40 participants from SickKids, and 25 from other sites in order to ensure distributed enrollment across sites and reduce the risk of health system bias.

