Given that the intervention is strategically implemented over three years to ensure that age and developmentally appropriate skills are being reinforced during the transition years spanning pediatric into adult care, the concern regarding patient attrition is present. Given the typically high degree of engagement, parental oversight and multi-disciplinary involvement in pediatric care, the attrition risk is likely highest during early adult care. The transition navigators will be aware of this concern and use more provider-initiated interactions to sustain adherence and engagement.

The issue of sustainability is a concern. Healthcare administrators and patients have been involved to understand implementation challenges. The cost and cost-effectiveness will be monitored through health resource utilization. Finally, international groups must adapt and evaluate the intervention in the setting of other healthcare systems.

Finally, it is possible that the control group will have better results because of repeated research measurements, ongoing monitoring, and increased awareness of transition as an important health issue. We have attempted to design the control protocol to mimic standard practice but realize that monitoring bias may occur. However, this would reduce the risk of Type 1 error and provide more argument for wide implementation if efficacy is demonstrated.

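### The handling of withdrawn participants is unclear, and the primary T3 rank test cannot use anyone without a T3 score, although 25% loss is expected and may differ by arm

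*Protocol article*

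**What the plan says.** On withdrawal, the article (Withdrawal criteria) says: "Participants who request study withdrawal will be removed and a withdrawal interview conducted". The next sentence treats non-adherence differently: "Non-adherence to the study intervention will be part of the data collected and analyzed and will inform program rollout".

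On the primary analysis, Statistical analysis sets the endpoint as the IBD-DI at the end of treatment, one to two years after transfer, and continues: "We will compare groups using the Wilcoxon-Mann–Whitney test, and statistical significance set at P < 0.05". No covariate or stratum adjustment is mentioned. The same section adds that "repeated measures analysis will determine changes over time for the primary and secondary outcome measures at three timepoints". This is described as additional to the primary test. Table 5 schedules the IBD-DI at enrollment (T1), transfer (T2) and study end (T3).

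On attrition, the sample size paragraph reads: "Assuming a drop-out rate of 25% in each group over the course of the study", and enrollment is set at 90. Limitations places the greatest attrition risk in early adult care and gives one remedy: "The transition navigators will be aware of this concern and use more provider-initiated interactions to sustain adherence and engagement". The description of the control group (end of Core component 4) limits controls' dealings with navigators to completing assessments. These are scheduled at enrollment, transfer and study termination.

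**The concern.** Three features of the plan act together.

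- **Status after withdrawal.** The article does not say whether a person who asks to leave keeps their T1 and T2 scores in the dataset, stays in the randomized group, or may still be approached for T3 or linked to health administrative data.
- **Choice of primary test.** A rank test at one time point has no place for a participant whose T3 score is missing, unless a value is imputed. The analysis that could use such a participant's earlier scores is planned, but is not primary.
- **Retention contact.** The one stated measure against attrition runs through the navigators, whose engagement work belongs to the intervention. Equal loss in the two groups is what the sample size assumes, but the retention design does not obviously deliver it.

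About 22 of 90 randomized participants may have no T3 score. If who is lost depends both on arm and on how the person is doing, the primary comparison is biased. Enrolling more participants does not correct that.

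**Working it through.** **1. The plan's own figures.** Inputs from the sample size paragraph: d = 0.78 (16 points over an SD of 20.5), alpha 0.05, 1:1 allocation, 25% loss. A noncentral-t calculation with the Wilcoxon-Mann–Whitney efficiency 3/π gives 23 per arm (46) for 80% power and 31 per arm (62) for 90% power, as stated, if the test is one-sided. Two-sided it gives 29 and 38 per arm. The article does not state sidedness; that is a separate matter.

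Allowing for loss: 62 / (1 − 0.25) = 82.7, so 83, which the target of 90 covers. Expected T3 scores: 90 × 0.75 = 67.5; expected losses: 90 × 0.25 = 22.5. With 33 to 34 per arm, power is about 92–93% one-sided or 86–87% two-sided. Precision is therefore covered. The open question is bias.

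**2. Shift in the observed contrast.** Let p be the proportion lost in an arm and δ the amount by which lost participants score worse (higher) than those observed. The observed mean is lower than the full-arm mean by p × δ. With the contrast taken as intervention minus control:

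shift = p(control) × δ − p(intervention) × δ

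The documents give only 25% in each group, so the 10% and both values of δ below are assumptions.

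| Control loss | Intervention loss | δ | Shift | Share of 16 points |
|---|---|---|---|---|
| 25% | 25% | any | 0 | 0% |
| 25% | 10% | 10 | 2.5 − 1.0 = 1.5 | 9% |
| 25% | 10% | 20 | 5.0 − 2.0 = 3.0 | 19% |

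A higher IBD-DI is worse, so a positive shift works against the intervention. If those doing well are the ones who leave, δ is negative and the shift favors the intervention. The unequal rows imply 45 × 0.25 + 45 × 0.10 = 15.75 losses, fewer than the 22.5 planned for.

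**3. Simulation under no true effect.** 45 per arm, normal scores, SD 20.5, probability of loss logistic in the unseen T3 score, two-sided Wilcoxon-Mann–Whitney test on those observed, 8,000 runs per scenario. OR is the odds ratio of loss per SD of worse T3 score. Loss rates by arm and ORs are assumptions; each scenario averages 25% loss.

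| Loss, intervention / control | OR, intervention / control | Bias (points) | Type I error |
|---|---|---|---|
| 25% / 25% | 1 / 1 | 0 | 5.1% |
| 15% / 35% | 1 / 1 | 0 | 4.9% |
| 25% / 25% | 2 / 2 | 0 | 5.0% |
| 15% / 35% | 2 / 2 | +2.5 | 7.2% |
| 10% / 40% | 2 / 2 | +3.8 | 11.1% |
| 15% / 35% | 3 / 3 | +3.5 | 11.4% |
| 15% / 35% | 0.5 / 0.5 | −2.5 | 7.7% |
| 25% / 25% | 2 / 0.5 | −6.5 | 24.9% |
| 25% / 25% | 0.5 / 2 | +6.5 | 25.4% |
| 25% / 25% | 3 / 0.33 | −9.3 | 48.8% |

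Unequal rates alone do no harm, and neither does outcome-related loss that is the same in both arms. Bias needs loss that is related to outcome and differs by arm, in its rate or in its mechanism. The last three rows are extreme cases that show how far opposite mechanisms could go. Nothing in the article says they will occur.

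**The case against.** A reader might infer that withdrawn participants' data are deleted, that the primary analysis is declared completers-only, and that retention effort exists in one arm only. The article supports none of these as stated facts.

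- Removal can mean leaving follow-up and nothing more. The next sentence keeps non-adherent participants in the data, so someone who stops the modules without leaving the study is not removed.
- No completers-only population is named. Analysis populations and missing-data rules commonly sit in the full protocol or SAP, so their absence here is no error.
- The Limitations passage on navigator contact names no arm. Controls have three scheduled assessments, checklists and yearly webinars, and more contact in the intervention arm is partly the treatment under test.
- Nothing says that withdrawn participants are excluded from the linked health data.
- The 25% is total loss. Requested withdrawals are an unknown part of it.
- The bias rests on assumed rates. In the simple example it is small (1.5 / 20.5 = 0.07 SD to 3.0 / 20.5 = 0.15 SD) and runs against the intervention.

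All of this stands, and it limits the point. It does not remove two facts that the article does state: the primary test is at a single time point, with the analysis that could use earlier scores placed second; and the only named attrition remedy depends on staff whom controls see only for assessments. Making the model primary is partly a preference, since the article calls the outcome ordinal and the model brings its own assumption about missing data. The case for it is that the data and the model are already planned.

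**Conclusion.** The point holds as a worthwhile improvement. The article contains no demonstrated error in the primary result. The withdrawal wording leaves the status of data and randomized group open. The primary test on its own cannot use the roughly 22 participants expected to lack a T3 score, and the article places the greatest attrition risk in the period when T3 falls. Retention contact is described in a way that may make loss differ by arm.

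Under the stated assumptions the shift is 1.5 to 3.0 points, with its sign depending on whether those doing badly or those doing well leave. Under moderately unequal, outcome-related loss in the simulation it is about 2.5 to 4 points in size, with type I error of 7% to 11%. It is zero if loss is unrelated to outcome, or alike in rate and mechanism in both arms. The documents do not show which situation will apply, so neither the size nor the direction can be predicted.

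**What to change.** 1. **Define removal.** State that it means stopping the intervention, follow-up or both; that data already collected and the randomized group are kept; and that T2 and T3 questionnaires and health-data linkage continue wherever consent for them stands. Record withdrawal from the program separately from withdrawal of consent for data.
2. **Collect T3 alike in both arms.** Use one research-staff reminder schedule for outcome questionnaires, independent of navigator contact. Automated REDCap reminders would do.
3. **Change the primary estimate.** Take the T3 effect from the planned repeated-measures model, with all participants as randomized, T1 as covariate, T2 and T3 as outcomes, and center included. If loss occurs mainly after transfer, many of those lost will already have a T2 score for the model to use.
4. **Sensitivity analyses.** Keep the Wilcoxon-Mann–Whitney test at T3, and add one analysis that departs from missing at random.

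The cost is wording in the protocol, consent form and analysis section, a reminder set-up for controls, and a little extra analysis. The model relies on missing at random, which is why the second sensitivity analysis is needed. The article says recruitment had not begun at submission; changes made before unblinded outcome data are examined carry the least risk.

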### Setting

Participants will be recruited from pediatric IBD centers that are part of the Canadian Children IBD Network (CIDsCaNN). Participants will be followed past transfer of care and, thus, the intervention will follow AYAs during their care by adult gastroenterologists. Since the intervention is decentralized and virtual, no resources will be required from the receiving adult gastroenterologists. Adult providers (gastroenterologist and family physicians) will be given clinically relevant updates on the participants in their practice by the transition navigator (core component 2). At the end of follow-up, the adult provider will provide a summary measure of disease activity (see Outcome Measures).

